**Fig. 1 fig1:**
[figure not shown]
PArTNER study design. In the PArTNER study, participants hospitalized with a physician diagnosis of heart failure, pneumonia, chronic obstructive pulmonary disease (COPD), myocardial infarction, or sickle cell disease are randomly allocated to one of two groups: Navigator intervention or Usual care. The Navigator intervention spanned over a 2-month period after hospital discharge and included: 1) community health workers (CHWs) who conducted in-person study visits in the hospital and a single home visit 1–3 days post-discharge to assess barriers to patient-centered transitions from hospital to home, and 2) peer coaches are introduced on hospital discharge and contact participants via telephone at approximately 1, 2, 3, 5, and 7 weeks post-discharge to continue supports initiated by CHWs. Following in-person baseline data collection prior to randomization, follow-up outcomes were assessed via telephone at 30 days and 60 days post-discharge.

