#### Primary outcomes

2.10.1

Patient and caregiver engagement activities indicated the need for two co-primary outcomes for the clinical trial:1.Change in participant anxiety from baseline (enrollment to 30 days post-discharge).2.Change in participant informational support (enrollment to 30 days post-discharge).

Informational support refers to the ability to obtain advice, guidance, suggestions, or useful information.

We will use the National Institutes of Health (NIH) PROMIS measures for our co-primary outcomes, since the development and validation of PROMIS scales have been extensively documented [27]. The PROMIS emotional distress-anxiety short form (version 1.0 SF4a, 4 items) will be used to assess participant anxiety in the previous 7 days. The PROMIS informational support short form (version 2.0 SF4a, 4 items) will be used to assess informational support among study participants in the previous 7 days. For PROMIS measures, raw scores for each measure will be re-scaled into a standardized T-score with a mean of 50 and standard deviation of 10 for the US general population [27,32,33]. Higher PROMIS T-scores indicate more of the concept being measured (e.g., higher anxiety T-scores indicate more anxiety). Studies suggest that a 2- to 5-unit or greater difference in T-scores is likely to be the MCID, though the MCID following hospital discharge in the target population has not been established.

Using PROMIS measures confers several distinct advantages: 1) *Comparability*—measures have been standardized to be patient-centered, rather than disease-specific, permitting comparisons of patient outcomes between the Navigator and Usual care groups despite enrolling patients with multiple conditions; 2) *Reliability* and *Validity*—metrics for each domain have been rigorously reviewed and tested; 3) *Flexibility*—PROMIS measures can be administered in a variety of ways (in person, telephone, or via computer adaptive testing); for PArTNER, the baseline visit occurred while the patient was in the hospital, so administration was in person. Follow-up visits were performed by telephone to minimize participant burden (a key principle in effectiveness trials); and 4) *Inclusiveness*—PROMIS encompasses all people, regardless of literacy, language, physical function, or life course.

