#### Secondary outcomes

2.10.2

Secondary outcomes include assessments of change in participant PROMIS anxiety and in informational support T-scores from enrollment to 60 days after hospital discharge, as well as changes of other PROMIS measures (instrumental support [version 2.0, SF4a, 4 items; emotional support [version 2.0 SF4a, 4 items], mental health [version 1.1 SF, 4 items within the 10-item global health scale], physical health [version 1.1 SF, 4 items within the 10-item global health scale]) from enrollment to 30 and 60 days after [27].

We will also assess healthcare utilization as secondary outcomes. We will assess attendance at outpatient clinics within 14 days of hospital discharge (using self-report; and separately using review of electronic health records at UI Health, which is shared with the hospital and all ambulatory clinics within health system, including a network of 11 federally qualified healthcare centers); death at 30 and 60 days after hospital discharge (based on caregiver report or review of electronic health records); rehospitalization at 30 and 60 days (assessed by review of electronic health records); emergency department visit at 30 and 60 days (assessed by review of electronic health records); death or re-hospitalization at 30 and 60 days; and finally, death or re-hospitalization or emergency department visit at 30 and 60 days. We do not have access to claims data to ascertain healthcare outside of the hospital or ambulatory clinics outside UI Health.

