### Analytical and statistical approaches

2.11

Analyses will be performed in three steps. *Step 1* consists of exploratory analyses to identify, correct, and confirm values or missing data, and provide descriptive statistics (frequency [proportions], mean [standard deviations]). *Step 2* focuses on bivariate analyses to compare primary and secondary outcomes by treatment group. We will use t-tests, Wilcoxon rank-sum tests, chi-squared tests, and Fisher's exact tests, as appropriate, for pairwise comparisons between the Navigator and Usual care groups. *Step 3* includes multivariable logistic or linear regression models, as appropriate, to account for potential confounders for the primary and secondary outcomes. The co-primary analysis is pre-specified as use of multivariable linear regression models comparing change in anxiety and change in informational support from enrollment to 30 days after hospital discharge in the Navigator group compared with the Usual care group, after adjusting for potential confounders (i.e., adjusted differences). We pre-defined potential confounders as baseline age (>65 years, yes/no), gender (women vs. men), race (non-Hispanic black vs. other), target health condition (pneumonia, heart failure, COPD, myocardial infarction, sickle cell disease), having a primary care provider (yes/no), patient-reported usual source of healthcare (doctor's office, emergency department, community health center, other), patient-reported hospitalization in the 12 months prior to index hospitalization (yes/no), education (high school or less vs. other), and health insurance (yes/no). To minimize the risk of bias in specifying potential confounders, we will examine the baseline characteristics of study participants while being masked to treatment group allocation before finalizing the list of potential confounders for the multivariable analyses.

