All analyses will be conducted using a modified intention-to-treat principle, in which we ignored the individual with the missing data for the co-primary outcomes (complete-case analyses). To assess the sensitivity of results to the complete-case analyses, we will conduct multiple imputations under a missing at random (MAR) assumption [34]. We will also conduct multiple imputations under a missing not at random (MNAR) assumption under a joint selection model of outcome and missingness and employ Bayesian analyses for each of the two co-primary outcomes. Our multi-tiered approach to missing data will be used to determine if the Navigator intervention effects are qualitatively maintained across various approaches to handling missing data. We will also conduct per-protocol analyses (PPAs) for the primary outcome. In the PPAs, the Navigator intervention will be considered per-protocol if the participant received both hospital and home-based components of the CHW-led interventions and at least one peer-coaching call. We will employ a 2-sided Bonferroni-corrected alpha of 0.025 (and 97.5% confidence intervals, CIs) for the two co-primary outcomes in the multivariable analyses, and a 2-sided alpha of 0.05 (and 95% CIs) for all other hypothesis tests.

We will also conduct exploratory analyses to assess the potential for heterogeneity of treatment effects for the primary outcome by examining the consistency of the adjusted differences in pre-specified subgroups (across levels of each baseline characteristic) in a series of linear regression models with covariates that included the treatment-group indicator, the treatment-by-subgroup interaction terms, and all other covariates in the multivariable models. We will also collect a limited number of baseline characteristics in keeping with information that is routinely collected on hospitalizations and that have been associated with hospital readmissions at MSIs [35]. The p-values for consistency of adjusted differences in linear or logistic regression models across subgroups will be determined by Wald chi-squared tests. The PArTNER study was not specifically powered to assess heterogeneity of treatment effects, so all such analyses should be considered exploratory. Due to multiple hypothesis tests, we will employ Bonferroni corrections to reduce the risk of a type 1 error.

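### Read literally, the complete-case rule in section 2.11 covers all analyses and so removes nearly all 30-day deaths, and every unreachable survivor, from the record-based outcomes

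*Protocol article*

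**What the plan says.** Section 2.11 sets the analysis population in one sentence: "All analyses will be conducted using a modified intention-to-treat principle, in which we ignored the individual with the missing data for the co-primary outcomes". The sentence covers all analyses. It removes the person, not just the missing value, and the trigger is missing co-primary data.

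Those data are the 30-day changes in PROMIS anxiety and PROMIS informational support; section 2.10.1 gives the second as "Change in participant informational support (enrollment to 30 days post-discharge". The Fig. 1 legend says that "follow-up outcomes were assessed via telephone at 30 days and 60 days post-discharge".

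Section 2.10.2 names mortality among the secondary outcomes, worded as "death at 30 and 60 days after hospital discharge (based on caregiver report or review of electronic health records"). Readmission is a separate secondary outcome there, worded as "rehospitalization at 30 and 60 days (assessed by review of electronic health records"). Visits to the emergency department come from the same records. One composite is "death or re-hospitalization at 30 and 60 days", and a further one adds emergency department visits. The paragraph before the rule describes logistic or linear models "to account for potential confounders for the primary and secondary outcomes", so secondary outcomes are among the analyses that the section covers. The article gives the record-based outcomes no other analysis set.

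Section 2.4 assumes 20% attrition and 565 participants per arm. It claims 80% power for a fall in 30-day death or re-hospitalization from 30% to 22.5%, and 90% power for a 10-point fall.

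**The concern.** Someone who dies before the 30-day call has no 30-day PROMIS score. Under the rule as worded, that person leaves the mortality analysis because they died. Thirty-day mortality becomes close to 0 versus 0, the 30-day composites lose their fatal part, and 60-day mortality counts only deaths after a completed 30-day interview.

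Living participants who cannot be reached are dropped too, although their records are available. The Discussion expects such losses from unstable housing and changing contact details. Being too ill to answer, or being back in hospital, could also prevent an interview. The readmission comparison would then be made in a subset chosen after randomisation by a criterion plausibly related to the outcome.

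These outcomes matter to the trial. Death or re-hospitalization helped to set the sample size, and the Introduction cites concern that reducing readmissions may increase deaths outside hospital.

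**Working it through.** **Inputs from the article.** 565 per arm, 20% attrition, and risks of 30% versus 22.5% (or 20%) are from section 2.4. Two-sided alpha of 0.05 for tests other than the co-primary ones is from section 2.11. The article gives no mortality rate and no response rate by outcome; every such figure below is an assumption.

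**Formula.** With n per arm and p̄ the mean of the two risks,

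power = Φ{ [ |p1 − p2| − 1.96·√(2p̄(1 − p̄)/n) ] / √([p1(1 − p1) + p2(1 − p2)]/n) }.

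**Step 1: reproduce the plan's figure.** p1 = 0.30, p2 = 0.225, p̄ = 0.2625, n = 565. The numerator is 0.075 − 1.96 × 0.02618 = 0.0237, the denominator is 0.0261, and power is Φ(0.908) = 81.8% (80.0% with continuity correction). The stated 80% is reproduced when everyone randomised is analysed.

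**Step 2: apply the rule with the plan's own attrition.** 565 × 0.8 = 452 per arm, so 1,130 − 904 = 226 people are dropped. At unchanged risks the numerator is 0.075 − 1.96 × 0.02927 = 0.0176, the denominator is 0.0292, and power is Φ(0.605) = 72.7% (70.2% with continuity correction). For 30% versus 20%, power is 97.3% with 565 and 93.6% with 452, so the 90% claim holds either way and does not help to settle which set was intended.

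**Step 3: deaths removed.** At an assumed 30-day mortality of 2%, 4% or 6%, 1,130 × rate gives about 23, 45 or 68 deaths. That is 7%, 13% or 20% of a 30% control-arm composite.

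**Step 4: effect on the estimate.** Assume deaths of 4% versus 2% and non-fatal rehospitalization of 24% in both arms. The true composite is 28% versus 26%, a difference of 2.0 points. With deaths dropped, the risks are 0.24/0.96 = 25.0% and 0.24/0.98 = 24.5%, a difference of 0.5 points.

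**Step 5: range of power for 30% versus 22.5% under the rule.** Unequal arm sizes are used where they arise.

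| Assumed pattern | Risks seen | n per arm | Power |
|---|---|---|---|
| Deaths 2% in both arms, effect wholly non-fatal | 28.6% v 20.9% | 452 | 76% |
| Deaths 4% in both arms, effect wholly non-fatal | 27.1% v 19.3% | 452 | 80% |
| Deaths 6% in both arms, effect wholly non-fatal | 25.5% v 17.6% | 452 | 83% |
| Interview completed by 65% with an event, 85% without | 24.7% v 18.2% | 446 and 455 | 66% |
| Deaths 6% v 4.5% with no response; otherwise 65% and 85% | 20.8% v 15.1% | 424 and 438 | 59% |
| Interview completed by 50% with an event, 90% without | 19.2% v 13.9% | 441 and 458 | 58% |

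In the first three rows the risks are (0.30 − d)/(1 − d) and (0.225 − d)/(1 − d), where d is mortality. In the fourth, the control risk is 0.30 × 0.65/(0.30 × 0.65 + 0.70 × 0.85) = 0.247, and the Navigator risk has the same form with 0.225 and 0.775; the sixth uses 0.50 and 0.90. These two rows apply one response rate to the whole composite and so do not treat deaths as certain non-responders. The fifth row does: the control risk is 0.24 × 0.65/(0.24 × 0.65 + 0.70 × 0.85) = 0.208 and the Navigator risk is 0.18 × 0.65/(0.18 × 0.65 + 0.775 × 0.85) = 0.151.

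**The case against.** The strongest reply is that the sentence is loosely worded and was meant only for the co-primary models. What follows it is mostly about missing PROMIS data: the plan will "employ Bayesian analyses for each of the two co-primary outcomes", and the per-protocol and subgroup analyses concern the primary outcome. Section 2.8 provides for record review of healthcare utilization separately from the calls. A plan that knowingly analysed only people interviewed at 30 days would hardly list 30-day death as an outcome, and the power figure in section 2.4 fits full analysis of everyone randomised. This makes a narrower intention likely. It does not change the text. The same section limits other analyses expressly to the primary or co-primary outcomes, while this rule is stated for all analyses and nothing exempts the record-based outcomes. Multiple imputation is offered as a sensitivity analysis, and nothing says that it returns excluded people to the death or readmission analyses, where their values are not missing in the first place. Nor is this a detail left to an analysis plan that is not shown: it is a stated rule that conflicts with stated outcomes and a stated power.

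A reader might infer more than the article supports:

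- That every 30-day death is certain to be excluded. No window is given for the call, so someone interviewed shortly before dying near day 30 could be retained.
- That power falls to a fixed 73%. That figure assumes unchanged risks after exclusion, and step 5 shows that the loss can be larger or can vanish.
- That mortality information is lost altogether. Section 2.8 collects reasons for loss, with death as its example, for the participant flow diagram, and section 2.9 provides a monitoring board that meets twice a year. Neither replaces a randomised comparison of mortality, but deaths would not go unseen.

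**Conclusion.** The point holds on the wording. Applied literally, the rule takes out of the death, rehospitalization, emergency department and composite analyses essentially everyone who dies before the 30-day call, and every survivor without that interview. It contradicts the listing of 30-day death as an outcome and the 80% power claim, which needs all 565 per arm.

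The main harm is the selection after randomisation and the lost deaths. It does not depend on any assumed rate, though its size does: about 23 to 68 deaths at 2% to 6% mortality. Power is 72.7% at 452 per arm with unchanged risks, and roughly 58% to 83% over the scenarios shown, which are illustrations and not bounds.

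The co-primary analyses are not affected by this point. The article does not show that the investigators intended to exclude deaths; it shows a rule that would do so if followed.

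**What to change.** Restrict the complete-case rule to the PROMIS outcomes and, for each one, exclude only participants missing that outcome. State that death, rehospitalization, emergency department visits, their composites and record-based clinic attendance are analysed in all randomised participants as assigned, whether or not the 30-day or 60-day interview was completed.

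The cost is one sentence in the protocol or analysis plan. No new data are needed, because these outcomes are already to be collected from health records or caregiver report. The analysis set would then agree with the power statement in section 2.4.

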##### CHW-led interventions (Table 2)

2.5.1.1

The CHWs interviewed participants in person during the index hospitalization and at a home visit within three days of hospital discharge. The goal of these CHW-led sessions was to identify barriers to health and healthcare and to provide support to promote self-management skills. Potential resources for participants will be accessed using an interactive online resources database that allowed identification of hyper-local resources to each unique participant [28]. The CHW intervention is flexible to allow it to occur via phone or around the time of follow-up appointments at UI Health if needed. The initial visit is scheduled to occur over approximately 45 min. The number of visits conducted by the CHW during hospitalization is dependent on participants’ needs and length of stay; participants will receive daily visits in some cases.

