##### Peer-coach-led interventions (Table 3)

2.5.1.2

The telephone-based peer coaching support at weeks 1 (intervention window 6–10 days), 2 (12–16 days), 3 (19–23 days), 5 (32–37 days), and 7 (47–51 days) after hospital discharge is intended to continue supports initiated by the CHW intervention (Fig. 1). Each peer coach call is scheduled for approximately 15 min, while each participant could have had more than one peer coach across the five calls (mimicking real-world circumstances). Patient advocacy organizations will provide peer coaching support for participants hospitalized with pneumonia or COPD (COPD Foundation), myocardial infarction or heart failure (Mended Hearts), and sickle cell disease (Sickle Cell Disease Association of Illinois) [[29], [30], [31]]. The “peer coaching” intervention by phone is intended to leverage existing services and to connect participants with resources in the community. The COPD Foundation has a well-developed peer coaching (patients with COPD or caregivers of patients with COPD) infrastructure that provides a method for tracking and recording peer coaching phone calls. If a peer coach is not available from the specified organization, the CHW would temporarily fill-in to complete peer coaching calls. Through the HIPAA-secure database, peer coaches have access to the CHW-completed *Barrier Assessments* and *Discharge Patient Educational Tool (DPET*; see online supplement) that is specific to their patients, helping to facilitate a team response and to know each participant's unique needs. Over the course of approximately 60 days post-discharge, peer coaches will use a sequence of up to five phone calls to provide support in addressing barriers to care and the use of the DPET to promote self-management. Up to four call attempts will be made for each peer coaching call (will attempt to leave voicemails after each unsuccessful call attempt).

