### Data collection and sources

2.8

The ascertainment of outcomes after hospital discharge will be performed by a trained research coordinator who is masked to treatment group allocation. The research coordinator will attempt to contact participants by telephone. Up to 14 call attempts will be made to collect patient-reported outcomes for each of the 30- and 60-day assessments. Electronic health records will also be reviewed to assess outcomes, particularly healthcare utilization, at 30- and 60-days post-discharge.

Many aspects of our study design are intended to reduce the frequency of missing data. We designed the study to target a population not adequately served by current services, which could help serve as an incentive for clinicians to support the study and for participants to remain in the study. We will accommodate individual preferences as much as possible when setting follow-up visits or data collection time-points. The study enrollment and data collection will be performed as participants receive routine care in the hospital and with reduced burden post-discharge (e.g., data collection by phone, rather than in-person). Also, we do not equate treatment discontinuation with study drop-out; we will encourage participants to continue in the study and provide outcomes data even if they no longer wish to remain in the treatment group assigned by randomization. We will also encourage participants to continue in the study by explaining the importance of completing the study with as many participants as were enrolled to avoid selection bias. Reasons for withdrawing from the study or lost to follow-up will be collected when possible by interviewing study participants, caregivers, and review of electronic health records (e.g., participant died), and reporting the information in a participant flow diagram.

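### The per-protocol rule for the 30-day co-primary outcomes accepts coaching calls scheduled after day 30, and its criterion for the Navigator arm alone leaves the contrast unprotected by randomisation

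*Protocol article*

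**What the plan says.** The protocol article, section 2.11 (Analytical and statistical approaches), states: "We will also conduct per-protocol analyses (PPAs) for the primary outcome". The rule that follows requires that the participant "received both hospital and home-based components of the CHW-led interventions and at least one peer-coaching call". It is worded for the Navigator intervention, and no matching criterion is given for Usual care.

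Section 2.10.1 (Primary outcomes) sets the time point, for example "Change in participant anxiety from baseline (enrollment to 30 days post-discharge", and likewise for informational support. Section 2.5.1.2 (Peer-coach-led interventions) schedules five calls. The first three have windows ending by day 23; the last two are at weeks "5 (32–37 days), and 7 (47–51 days) after hospital discharge".

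On how the community health worker (CHW) component is delivered, section 2.5.1.1 says: "The CHW intervention is flexible to allow it to occur via phone or around the time of follow-up appointments at UI Health if needed".

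**The concern.** Exposure that defines treatment status should come before the outcome it is meant to explain. Here any one of the five calls qualifies, including two whose windows open after day 30. A Navigator participant who missed the first three calls and answered the fourth or fifth would enter the 30-day per-protocol set, although no coaching preceded the nominal outcome. Membership of the set would then depend partly on being reachable after the outcome was measured.

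A second issue lies behind this. Qualifying depends on post-randomisation contact (a home component and an answered call) and is required in one arm only. Section 3 (Discussion) names unstable housing and unreliable telephone contact as reasons participants may not be reached. If those traits also relate to change in anxiety or informational support, the selected Navigator participants are no longer comparable with the Usual care arm. At stake is the reading of the analysis that comes closest to asking whether the intervention works when delivered.

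**Working it through.** **Design figures used as a yardstick.** The per-protocol rule has no figure of its own. Section 2.4 (Power and sample size) gives 565 per arm, 20% attrition, two-sided alpha 0.025, a target of 2.5 T-score units and, since 2.5 is 25% of a standard deviation, SD = 10. Evaluable per arm: 565 × 0.8 = 452. Power recomputed at 452 per arm is 93.5%, close to but slightly below the stated 95% or greater. It is used here only to fix SD, target and numbers.

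**1. Calls against the outcome date (sections 2.5.1.2 and 2.10.1).**

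| Call | Window (days after discharge) | Against day 30 |
|---|---|---|
| Week 1 | 6–10 | before |
| Week 2 | 12–16 | before |
| Week 3 | 19–23 | before |
| Week 5 | 32–37 | opens 2 days after |
| Week 7 | 47–51 | opens 17 days after |

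Two of the five qualifying calls (40%) are scheduled after the nominal outcome. The PROMIS items ask about the previous 7 days (section 2.10.1), so a day-30 answer cannot reflect later coaching.

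**2. How many participants this could involve.** The document gives no call completion rate. Assume each call is completed independently with probability p. Among those with at least one call, the share whose first call is at week 5 or 7 is

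[(1 − p)^3 − (1 − p)^5] / [1 − (1 − p)^5].

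For p = 0.3: (0.343 − 0.168) / (1 − 0.168) = 0.175 / 0.832 = 21%. Over the range: 27% (p = 0.2), 21% (0.3), 15% (0.4), 10% (0.5), 5% (0.6), 2.5% (0.7). With completion varying between persons (beta-distributed, mean 0.3 to 0.7), the share is about 5% to 13%. None of these figures conditions on having completed the home component.

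**3. Selection in one arm, no true effect.** Let a fraction p of the Navigator arm qualify, let the propensity to qualify correlate r with the outcome, and leave Usual care unrestricted. The spurious difference is SD × r × φ(z_p)/p. With p = 0.6, φ(0.253)/0.6 = 0.644, giving 0.64, 1.29 and 1.93 units for r = 0.1, 0.2 and 0.3. These r values are assumptions, and so is the sign.

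This overstates the contrast in one respect: the analysis is complete-case, so Usual care is also filtered by answering the outcome call. A null simulation allowed for that, with 80% observed in both arms and a reachability trait correlating 0.6 with both qualifying and outcome response. Absolute bias in T-score units, for qualifying fractions from 80% down to 40%:

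| Correlation of reachability with outcome | Bias, complete cases | Bias, no outcome filter |
|---|---|---|
| 0.1 | 0.16–0.45 | 0.23–0.57 |
| 0.2 | 0.32–0.95 | 0.45–1.17 |
| 0.3 | 0.45–1.39 | 0.63–1.75 |

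The complete-case filter removes about 19% to 30% of the bias (1.17 to 0.95; 0.23 to 0.16) and does not eliminate it. The modified intention-to-treat contrast stayed between −0.03 and 0.02.

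**4. Delivery mode.** Section 2.5.1.1 allows the CHW contact by telephone or around clinic appointments. Section 2.11 requires a *home-based* component. Read literally, a permitted form of delivery would fail the per-protocol rule.

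**The case against.** The per-protocol analysis is supportive and decides nothing; the co-primary test is the adjusted modified intention-to-treat comparison. That stands, and it limits the weight of the point. The Discussion also warns that a clear relation between outcomes and the amount of intervention received may not be established.

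The analysis plan is not shown and may add a time limit or define the Usual care comparison set. That is fair for the comparator, which the article does not spell out: an unrestricted Usual care arm is read from the fact that a criterion is given for Navigator only. An adherence rule for one arm is also ordinary when the other has nothing to adhere to. The qualifying call is different, because the article states the rule, and as stated it has no time limit.

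No window is given for the 30-day assessment, and section 2.8 says: "Up to 14 call attempts will be made to collect patient-reported outcomes for each of the 30- and 60-day assessments". Some assessments may therefore follow a week-5 call. This is right for week 5 and much less plausible for week 7. The late-call group may also be small, since "Up to four call attempts will be made for each peer coaching call" and members must have missed three calls but completed the home component.

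The section 2.11 covariates (usual source of care, primary care provider, education, insurance, prior hospitalisation) may absorb some of the selection. None measures telephone reachability or housing stability. The word *home-based*, set beside hospital, may simply mean post-discharge.

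A reader might infer that the per-protocol result will favour Navigator and could be significant with no true effect. The document does not support that. With 271 (0.6 × 452) against 452, the critical difference at alpha 0.025 is about 2.24 × 10 × √(1/271 + 1/452) = 1.72 units. In the unfiltered formula the expected shift reaches this only if r exceeds 1.72/6.44 = 0.27. Both r and its sign are assumed. The timing fault taken alone would more naturally dilute a contrast than inflate it.

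**Conclusion.** The timing fault holds on the article's own wording: two of the five calls that can confer per-protocol status are scheduled after the nominal day-30 outcome. The number affected is unknown; 2.5% to 27% of those with at least one call is a range under an assumed completion rate of 0.7 down to 0.2 with independent calls.

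The one-arm selection concern holds as a mechanism. The contrast is not protected by randomisation and can be biased by reachability. Under the assumptions simulated, the bias was 0.16 to 1.39 units, at most about half of the 2.5-unit target (1.39/2.5 = 56%), but neither size nor direction can be derived from the document. The *home-based* wording needs clarifying and is no more than that. The co-primary modified intention-to-treat analysis is not touched.

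**What to change.** 1. For the 30-day co-primary outcomes, count a coaching call only if it was completed before that participant's actual 30-day assessment (nominally weeks 1–3). This also settles a week-5 call that precedes a late assessment. The cost is a sentence and a somewhat smaller per-protocol set. It does not cure selection: a stricter filter can increase it (in the formula above, lowering p from 0.6 to 0.5 raises the multiplier from 0.64 to 0.80).

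2. Label the per-protocol contrast supportive and non-randomised, and state which Usual care participants it uses. The cost is wording only.

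3. Reconcile the *home-based* requirement in section 2.11 with the delivery modes allowed in section 2.5.1.1, so that the rule says which contacts count.

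4. Optional: a complier-average estimate with randomisation as instrument. Non-qualifiers may still receive hospital CHW visits, the discharge education tool or the home visit, which strains the exclusion restriction. If 60% qualify, the intention-to-treat difference is multiplied by 1/0.6 = 1.67 and credited wholly to full compliers. If used, that assumption must be stated and the intervals will be wider.
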